#### Population survey

A cross-sectional survey of child-caregiver dyads will be conducted at four timepoints: at baseline (Step 0; mos. 1–3) and again at the end of each consecutive step, with 7 months between data collection rounds. Eleven children aged 4.5–5.5 years and their caregivers will be enrolled in the population survey from each of the 99 clusters (1089 child-caregiver dyads total), regardless of the child’s enrollment in the LEAPS preschool program. The primary objective of the population survey will be to assess changes in the average school-readiness over time. With this trial design, rather than assessing program impact on specific individuals, we are aiming to assess the impact of LEAPS on local (cluster-level) school readiness, which is a function of both the proportion attending LEAPS and the impact on the treated. By including both LEAPS participants and children who are not participating in the LEAPS program, this design will allow us to separate treatment effects on the treated from average (intent-to-treat) effects at the population level. The sample will be drawn from village birth registries provided by NCHD, which will be verified (a) by cross-checking against birth registries from local community health workers; and (b) through household visits conducted by research team members. The sample will be re-drawn at each of the four data collection timepoints. Children may be enrolled for assessment at multiple timepoints. Assessors will use a random number generator to select 11 participants/cluster using the verified lists of eligible children prepared for each cluster. If a participant refuses, assessors will select the next participant in the random sequence.
Eligibility criteria: Child is age 4.5–5.5 years ± 2 weeks (i.e., 53.5–66.5 months at the time of the survey) and resides in the targeted villageExclusion criteria: Child or caregiver shows signs of severe clinical health condition or disability

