### Sample size and power calculation for stepped wedge cluster-randomized trial

A power calculation was conducted with respect to the changes in average child outcomes using representative population surveys, applying the methods as outlined by Hemming and Taljaard [70]. The primary study outcome is children’s school readiness as indexed by scores on the International Development and Early Learning Assessment (IDELA). An intraclass correlation coefficient (ICC) of 0.175 was calculated based on the results of the LEAPS efficacy trial [26] using total IDELA score at endline for the control group. With a fixed number of clusters (*n* = 99) and a step-size of three (*n* = 33 clusters randomized per step), we estimate that at least 8 children per cluster per round, or 792 children total per round, will need to be enrolled to detect a 0.3 SD effect size at 80% power. To achieve adequate power and take refusal rate into account, we will enroll 11 child-caregiver dyads per cluster for a total of 1089 child-caregiver dyads per round, which should detect a 0.3 SD effect size at 90% power with full recruitment. In other words, we estimated sufficient sample sizes to achieve at least 80% power with up to 30% refusal/under-recruitment rate in each round of the data collection under the intent-to-treat principle. This includes refusals from caregivers and children, or under-recruitment due to a decrease in children available at the point of data collection, particularly in smaller villages.

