### Analysis

#### Impact evaluation

The primary analysis will use the intent-to-treat principle. Baseline balance will be tested between randomized groups to see whether randomization was successful. The primary outcome, IDELA total score, will be computed for each individual using the parameter estimates from the Graded Response Model, as recommended by the tool developers. We will assess the effect of the LEAPS intervention using the analytical framework proposed by Hussey and Hughes [71] for analysis of stepped wedge cluster-randomized trials. Estimation of treatment effects will be obtained from a generalized linear mixed model (GLMM) to produce the mean difference in IDELA scores for LEAPS intervention versus control. The GLMM will include a fixed effect for stratified randomization group, a random effect for cluster, a fixed effect for time, and use an exchangeable correlation structure. In addition, the study will perform a set of sensitivity analyses to explore potential deviations from the basic SW-CRT model proposed by Hussy and Hughes [71]. The closed school cohort data will be to examine the changes in the average school readiness among children participating in the LEAPS preschool between baseline and endline. Longitudinal data collected for school cohort participants will be linked using participant IDs. The preschool classroom structural and process quality data and the child household characteristics will serve as predictors of interest in adjusted analyses. Youth cohort data will be analyzed to examine differences in outcomes over time among CYLs as compared to the youth comparison group. Longitudinal youth participant data will be linked using participant IDs. Analysis will account for CYLs’ length of program exposure and adjust for potential confounding variables, including age, education, marriage status, assets-based household socio-economic status, and household food insecurity. No interim analyses are planned.

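### The primary mixed model fixes the cluster autocorrelation at 1 without support; if the true value is materially lower, its standard error is too small and type I error exceeds 5%

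*Protocol article*

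**What the plan says.** The Impact evaluation section of the protocol article sets the primary analysis "using the analytical framework proposed by Hussey and Hughes [71] for analysis of stepped wedge cluster-randomized trials". The model is a GLMM for the IDELA total score with a fixed effect for randomization stratum plus "a random effect for cluster, a fixed effect for time, and use an exchangeable correlation structure". No cluster-by-period effect, decaying correlation or robust standard error is named. The same section adds that "the study will perform a set of sensitivity analyses to explore potential deviations from the basic SW-CRT model", without listing them.

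The data come from repeated village surveys (Population survey). There are four rounds, "with 7 months between data collection rounds". "The sample will be re-drawn at each of the four data collection timepoints", and "Children may be enrolled for assessment at multiple timepoints".

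The sample size section has 99 clusters in three groups of 33, 11 children per cluster per round, and an ICC of 0.175 from the endline control data of the pilot trial.

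**The concern.** A single random intercept per cluster makes the correlation between two children of a village the same whether they are assessed in the same round or three rounds apart. The ratio of the between-round to the within-round correlation, the cluster autocorrelation, is thereby set to 1.

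The pilot ICC was measured at one timepoint, so it says nothing about correlation across rounds. The article also gives some reason to expect village-specific movement over time: its Limitations section names flooding and emergency shutdowns as risks. Where such events hit some villages and not others, a common fixed time effect does not absorb them.

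If such variation exists and the model omits it, the model counts the 11 children in a village-round as more independent information than they are. The standard error of the treatment effect is then too small, and the primary test and 95% interval miss their nominal levels. The unnamed sensitivity analyses would leave the primary interval and p-value as they are.

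**Working it through.** **Inputs from the article.** 99 clusters in 3 sequences of 33; 4 rounds 7 months apart, so first to last is 3 × 7 = 21 months; m = 11 children per cluster per round (8 as the stated minimum); ICC 0.175; target effect 0.3 SD.

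**Assumed, because the article does not give them.** Two-sided alpha 0.05; cluster autocorrelation (CAC) between 0.5 and 1; total variance 1.

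**The plan's own figure.** The article states 80% power at m = 8 and 90% at m = 11. Power = Φ(0.3/SE − 1.96), with the Hussey-Hughes variance for 99 clusters:
- m = 8: SE 0.0590, 0.3/0.0590 − 1.96 = 3.12, power 99.9%.
- m = 11: SE 0.0508, 0.3/0.0508 − 1.96 = 3.95, power above 99.9%.

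The stated 80% and 90% are not reproduced, and no variant tried gave both within 2 points. That is a separate matter and does not bear on this one.

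**Step 1, true covariance of village-round means.** Variance = ICC + (1 − ICC)/m = 0.175 + 0.825/11 = 0.175 + 0.075 = 0.250. Covariance between rounds = CAC × 0.175, for example 0.140 at CAC 0.8. The remaining 0.175 × (1 − 0.8) = 0.035 is shared by all children of one village in one round.

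**Step 2, what the planned model reports.** Find the variance components to which the random-intercept model converges under this truth. Then compare its model-based SE with the true (sandwich) SE of the same estimator.

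**Step 3, actual level.** Type I error = 2 × [1 − Φ(1.96 × SE_model/SE_true)].

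Results at m = 11, ICC 0.175, no repeat children:

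| CAC | Model SE | True SE | Ratio | Type I error | 95% CI coverage |
|---|---|---|---|---|---|
| 1.0 | 0.0508 | 0.0508 | 1.00 | 5.0% | 95.0% |
| 0.95 | 0.0509 | 0.0534 | 1.05 | 6.2% | 93.8% |
| 0.9 | 0.0511 | 0.0559 | 1.10 | 7.4% | 92.6% |
| 0.8 | 0.0513 | 0.0606 | 1.18 | 9.7% | 90.3% |
| 0.7 | 0.0515 | 0.0647 | 1.26 | 11.9% | 88.1% |
| 0.5 | 0.0519 | 0.0718 | 1.38 | 15.7% | 84.3% |

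Rough hand check at CAC 0.8: the round-specific noise of a village mean is 0.075 + 0.035 = 0.110, against 0.075 if there were no such variation, and √(0.110/0.075) = 1.21. The fitted model absorbs a little of the excess into its residual variance, which brings the ratio to 1.18.

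**Step 4, checks and sensitivity.**
- Simulated REML fits (4,000 runs each): 4.6%, 7.7%, 10.5% and 16.1% at CAC 1, 0.9, 0.8 and 0.5.
- Correlation that decays by round instead of dropping once: 7.6%, 10.2% and 16.7% at 0.9, 0.8 and 0.5 per round.
- m = 8, ICC 0.175: 6.6% at CAC 0.9 and 8.2% at 0.8.
- ICC 0.10, m = 11: 6.2% at CAC 0.9 and 7.4% at 0.8.
- ICC 0.05, m = 11: 6.0% at CAC 0.8.

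**Step 5, repeat children.** The age window is 66.5 − 53.5 = 13 months. A child can be eligible in two adjacent rounds (7 months apart) but not in rounds 14 months apart. If ages are spread evenly, (13 − 7)/13 = 6/13 of eligible children are still eligible at the next round. With an assumed adjacent-round overlap of 20-42% and a within-child correlation of 0.5-0.7, type I error becomes 3.1-4.4% at CAC 1, 4.3-5.5% at 0.95, 5.4-6.7% at 0.9 and 7.8-9.1% at 0.8.

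**Step 6, power with a cluster-by-period term, m = 11.** At CAC 0.8 the SE is 0.0603: 0.3/0.0603 − 1.96 = 3.02, power 99.9%. At CAC 0.5 the SE is 0.0705: 0.3/0.0705 − 1.96 = 2.30, power 98.9%.

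**The case against.** A reader might infer that the primary interval will be too narrow in any case. The article does not support that. It reports no between-round correlation, and at an autocorrelation of 1 the planned model holds its level.

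Repeat sampling works the other way. Re-sampled children raise the correlation between adjacent rounds, and near an autocorrelation of 1 this can make the planned test slightly conservative. That stands, and it is why the figures must be given as conditional. It does not remove the inflation at 0.8.

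The ICC is also fragile: the pilot had only five villages per arm, and adjustment for stratum may lower the ICC further. At a lower ICC the inflation shrinks. This stands too, but 0.175 is the value on which the trial was sized.

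Some possible sources of village-by-round variation are weak. A school calendar common to all villages is absorbed by the fixed time effect, and assessor drift is limited by the training and agreement checks in the data collection section. Only variation specific to a village and round counts.

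Finally, a reader might fault the article for not listing its sensitivity analyses or its standard error estimator. That would be unfair: such detail is commonly left to the full protocol or analysis plan, neither of which is shown, and the article does not rule out robust standard errors. If they are already planned there, the point is largely met. What the article does fix is the primary random-effect structure, and a sensitivity analysis does not change the primary result.

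**Conclusion.** The point holds conditionally. The primary model as stated assumes a cluster autocorrelation of 1 over rounds up to 21 months apart, and nothing in the article supports that assumption. If the true value is materially below 1 and model-based standard errors are used, the primary test is anti-conservative. With ICC 0.175, 11 children per cell and no repeat children, the level is roughly one and a half times nominal at 0.9 (7.4/5 = 1.5), about twice at 0.8 (9.7/5 = 1.9) and about three times at 0.5 (15.7/5 = 3.1).

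The size rests on autocorrelations assumed here, on the pilot ICC, and on how many children recur between rounds. A lower ICC or substantial overlap reduces it. At an autocorrelation of 0.95 or above with overlap, it may vanish or reverse.

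**What to change.** Add a cluster-by-period random effect to the primary GLMM, or use standard errors robust to clustering by village, or do both. With 99 clusters, robust standard errors are workable, and they also cover children assessed in more than one round, which a cluster-by-period term alone does not. Keep the basic exchangeable model as a named sensitivity analysis, so that its result can be compared with the primary one.

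The cost is one line of model specification, with no change to design or data collection. Intervals will be somewhat wider if the extra variance is real. By the formulas above, power for 0.3 SD at 11 children per cell remains about 98.9% or more for an autocorrelation of 0.5 or above.

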#### Implementation and systems readiness evaluations

Secondary administrative data for program monitoring will be analyzed using Excel and Stata to examine trends in program quality indicators over time and by subgroups (e.g., district, FO, CYL). Translated transcripts of the semi-structured IDIs and FGDs will be analyzed through a thematic analysis. Team members will independently review transcripts, followed by a combination of inductive and deductive coding and discussion to identify themes. A codebook and coding matrices will be constructed to support coding and analysis. Triangulation between stakeholders and data sources will be analyzed to understand both converging patterns and unique perspectives.

#### Cost evaluation

A cost analysis will be conducted to estimate total project costs for all stakeholders, in addition to cost per beneficiary and cost per impact. Costing data will inform NCHD efforts for expansion and replication of LEAPS.

## Ethics and dissemination

### Protocol amendments

All modifications to the protocol will be communicated with the PI, co-PI, and co-investigators through regular meetings and email communications. Any amendments to the protocol that have implications for the study design or participant safety will be reported to the affiliated ethics review boards through applications and email communications and to the trial registry through the application process. Protocol amendments impacting trial participants will be communicated in-person by the field research manager, evaluation field lead, or trained assessors.

### Reporting and risk of adverse events and harms

The LEAPS research team will be responsible for monitoring regulatory documents and participant files, including reviewing and maintaining all required ERC/IRB documentation, monitoring and updating regulatory supporting documents, recording meeting minutes, documenting the recruitment, enrollment, and informed consent processes, and maintaining logs to track data collection and assessment activities.

There is a small risk of loss of confidentiality for participants. To minimize this risk, interviews will be conducted in private spaces; tablets will be password protected; hard copies of forms will be stored in locked cabinets; data will be de-identified prior to sharing; and assessors will receive training in good clinical practice.

There is additionally a risk of psychological discomfort for youth participants due to survey questions on depressive symptoms. There is minimal risk associated with administration of the child assessments for executive function skills and school readiness and the household questionnaire with caregivers. To mitigate these risks, assessors are trained in how to sensitively administer youth and child assessments, and how to communicate with children’s parents about the assessment and their child’s performance. Participants will be informed that they may stop at any time without consequence.

The youth participant questionnaire includes a question on suicidal ideation. If the participant responds positively to this item, the assessor will contact the evaluation field lead and field research manager who will assess whether there is an imminent danger of self-harm. If there is immediate danger, then the assessor will escort the participant to a health provider. The team will also discuss with a consultant at the Aga Khan University Department of Psychiatry as needed. In no instance will the person be left alone. If the person has suicidal ideation, but is not at risk of immediate self-harm, the study staff will make an active referral for mental health care.

Finally, corporal punishment is unfortunately widely accepted in the intervention communities, so there is a risk that CYLs may initially use harsh disciplinary practices in the LEAPS classrooms. To mitigate this risk, CYL training includes preschool behavior management, covering strategies for appropriate classroom management and employing gentle discipline. The NCHD’s CYL contracts also include a clause prohibiting use of corporal punishment. If a CYL is observed using harsh discipline in the classroom, she will receive targeted training in classroom management. Repeated episodes of harsh discipline by a CYL will result in termination of the CYL’s employment.

### Consent to participate

For all data collection activities, informed consent will be obtained from participants by the research team’s assessors, who have received Good Clinical Practice training. For participants under age 18 years, both child assent and consent from a legal guardian will be obtained by a trained assessor. Consent forms were written to explain the information with accuracy and clarity for individuals with low levels of literacy (on average mothers in this location have 2 years of formal education) [26, 72]. All forms are written in Sindhi, the local language. All subjects will be free to withdraw from the study at any time and will be assured that this will not affect the standard of care received in the community.

Consent for the preschool classroom observations and video recording will be obtained by a trained assessor from the CYL/comparison preschool teacher, as well as a representative from the school’s parent-community board. For schools that do not have a parent-community board, the assessor will instead seek consent from the school’s leadership, i.e., the school principal or coordinator. Consent will be required from both the CYL/comparison preschool teacher and the representative from the school board or school leadership in order to proceed with the video recordings. The assessor will then enroll the CYL/teacher at the school and observe the classroom session to complete the assessment.

### Confidentiality

All assessments will be conducted in a private location, either in an assessment center, classroom, office, or private household. All data (including recorded interviews and notes, direct assessments, questionnaires, video recordings for quality assurance) will be de-identified by the research team. The keys linking identifiers to participants will be stored in a password-protected file (separated from the other data files), to which only the research team members will have access. All hard copy materials containing identifiable information (i.e., consent forms, interview cover sheets, photos) will be stored in locked cabinets. All tablets used for data entry will be password protected. Tablets and video recorders will be stored in locked cabinets when not in use. Data will be regularly transferred to the central server at Aga Khan University and then wiped. Video and audio recordings will be deleted after analysis is completed (within 1 year of endline). All research team staff will receive training in protecting participant privacy and adherence to Good Clinical Practices.

### Ancillary and post-trial care

Given that LEAPS serves vulnerable populations with limited access to education, training, and employment, the research team has a responsibility to ensure that LEAPS participants are supported beyond the trial period. The research team will coordinate with NCHD to ensure that (a) LEAPS children have a clear pathway to transition to primary school at the close of the trial and (b) that CYLs are supported through career counseling exit meetings to identify further options for education and employment.

### Dissemination: trial results

Results will be disseminated through a variety of channels, including workshops with government stakeholders, funder and lay reports, presentations at national and international conferences, publications in peer-reviewed journals, and through networks for early childhood and youth development such as Asia-Pacific Regional Network for Early Childhood, the Pakistan Alliance for Early Childhood, the Early Childhood Development Action Network, Early Childhood Peace Consortium, and the Alliance for International Youth Development.

## Discussion

This will be the first larger-scale impact evaluation of a youth-led ECCE program in an LMIC, providing much-needed empirical support for the youth-led ECCE model. The results of this evaluation will enable Pakistan’s NCHD to make evidence-based decisions about strengthening and expanding their community-based preschool and youth vocational training systems. The evidence from this evaluation will also be of relevance to regional and global settings where there is a vast unmet need for preschool services and limited employment and learning opportunities for youth. This study will additionally contribute to the literature around capacity development to support sustainable transitions of programming from donors to government ownership with changing levels of support technical partners, providing evidence from a systematic approach to capacity building and program transition with government partners in a rural, resource-limited context. It is our vision that this trial will lay the groundwork for future efforts to expand and replicate LEAPS in other NCHD communities, in order to strengthen NCHD’s ECCE programming on a wider, systems level. Figure 5 depicts the end goal for a fully integrated LEAPS program model, linked to NCHD Feeder Primary Schools within the Universal Primary Education Program. An expanded program model would additionally aim to obtain accreditation for CYL vocational training. Finally, findings from this work will contribute to the research around gender equity and youth development, providing a rigorous evaluation of a female-specific youth development program in an LMIC, a context for which there are very few program evaluations [18].

**Fig. 5 Fig5:**
[figure not shown]
NCHD Universal Primary Education Program (UPE) Feeder School and LEAPS Programs, Under Scale-up. This diagram presents the vision for the NCHD Universal Primary Education program structure including the Feeder schools and LEAPS schools under scale-up; KDI = Key Development Indicator; NCHD = National Commission for Human Development; SDG = Sustainable Development Goals

